#### Secondary outcomes

**Performance** of the instruments by clinical setting: seven frailty assessment tools will be used in four different levels of care. The performance of each scale in the classification of frailty will be established.**Feasibility** composed by two main conditions: the percentage of people that are assessed by each tool in each setting (adequacy) and the time for carrying out the tool assessment. The utility of both screening and diagnostic tools stems, among other characteristics, from the time needed to pass them. This characteristic is relevant mainly in settings where the demand for attention is high and the time to provide is limited.**Sensitivity to change**, one of the problems of many of the tools used to assess frailty is that they have a low sensitivity to change. This is a relevant issue in clinical settings, where monitoring the progress of the patient is of high value. For this purpose, we will evaluate the change in the assessment level of patients observed at 12 and 18 months with each of the tools and their correlations with the changes observed in the functional status of the patients as assessed by SPPB.**Qualification as screening and/or diagnosis tool**: evaluate the utility of each scale as a frailty detection method, using pre-established criteria, based on the prevalence of this condition in each setting and the classification performance (Sensitivity, Specificity, Positive and Negative Predictive Values and Likelihood ratios), plus its feasibility, and its sensitivity to change.

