In order to determine the sample size, we have used two assumptions:The sample size is calculated according to the methodology of Peduzzi et al. [21] for a model of 4 variables. The variables included are: age, gender and Charlson index as covariates and frailty status as the main independent variable of interest.The outcomes to be assessed will be death, falls, disability and deterioration in cognitive function. Among these variables, death is the least frequent and generates the highest sample size therefore it can be used for the other three outcomes.Although there are some little differences in the mortality rates among the five European countries that participate in this project; the mean mortality rate for people aged ≥75 years in these countries is 10% annually. Therefore, in 18 months it will be 15%, which is the follow-up period forecasted in FRAILTOOLS project.

Within these assumptions the lower limit of the 1-α confidence interval for the accepted number of success is 355 and 388 participants in each setting of care for 95 and 99% CI, respectively. This number must be increased with the forecasted lost to follow-up, in 20%. As a whole, the final sample size is established in 485 persons per setting, which means a final figure of 1940 persons. Thus, every partner will be responsible for the enrolment, assessment and follow-up of 388 older adults (97 per setting).

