### Statistical analysis

FRAILTOOLS aims to 1) assess the selected instruments (scales) for both screening and diagnosis purposes in each of the four settings: acute geriatric wards, geriatric outpatient clinics, primary care centers and nursing homes; and 2) explore the sequential or consecutive assessment of the older population amongst settings.

Regarding the first objective of the analysis, we will assess the associations of each of the seven scales with the outcome for each setting and outcome through logistic regressions using age, sex and Charlson index as possible confounders. With these variables, we will construct three logistic regression models: unadjusted, adjusted by age and gender, and adjusted by age, gender and Charlson Index. Firstly, we will compute the classification performance (sensitivity, specificity, ROC curve, AUC, predictive values, likelihood ratios) for each model. This way, we will assess the most accurate scale for both screening (the most sensitive tool) and diagnostic purposes (the most specific tool), for each setting and for each outcome. Secondly, we will study the feasibility of the models, considering the time needed for the scale and the percentage of patients that can be evaluated per case.

Combining both outcomes by creating an index (classification performance * proportion of evaluated patients), we will determine the best scale (maximum value of the index) per setting for both screening and diagnosis. Thirdly, we will evaluate the sensitivity to change of the scales and the covariance of the scales with other measures as the SPPB through a mixed linear model.

For the second objective, we will first analyze the external validity of each model by using the data of each setting in the other models during the last phase of the project. Afterwards, we will evaluate which set of instruments is more appropriate for sequential or consecutive assessment when patients move between different settings: e.g. from nursing homes to geriatrics wards.

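### The index that names the best scale multiplies an unspecified accuracy measure, not zeroed at no information, by the proportion evaluated, so an easily completed but weaker scale can outrank a better one

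*Protocol article*

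**What the plan says.** The Statistical analysis section fits, for each scale, setting and outcome, "three logistic regression models: unadjusted, adjusted by age and gender, and adjusted by age, gender and Charlson Index". It then says "we will compute the classification performance (sensitivity, specificity, ROC curve, AUC, predictive values, likelihood ratios) for each model". From these results it identifies "the most accurate scale for both screening (the most sensitive tool) and diagnostic purposes (the most specific tool", by setting and by outcome. Feasibility is studied next, as the time a scale takes and the share of patients who can be evaluated. Under Secondary outcomes that share is defined as "the percentage of people that are assessed by each tool in each setting (adequacy".

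The two parts are then joined by "creating an index (classification performance * proportion of evaluated patients), we will determine the best scale (maximum value of the index". The rule is applied per setting, for screening and for diagnosis. The article does not say which performance measure, or which of the three models, supplies the first factor. It subtracts no chance value and sets no minimum accuracy.

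**The concern.** A product of accuracy and completion ranks scales fairly only if a scale without information scores zero on the accuracy factor. Otherwise part of every score is earned by being completed. Each lost percentage point of completion is also charged against the whole accuracy value, not just the part above chance.

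The distortion favours tools that are easy to complete. The section on questionnaires makes differences in completion plausible: the FRAIL scale needs no measurements, the Fried criteria need grip strength and gait speed, and the 35-item index includes serum vitamin D.

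At stake is the scale recommended for each setting, which the Discussion intends for daily practice and for diagnostic algorithms. The misranking comes from the formula, so it would occur even if every input were known without error.

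**Working it through.** **Inputs.** The article states no value of the index, so there is no figure to reproduce. The formula comes from the Statistical analysis section. The outcome frequency, 15% mortality at 18 months, comes from the sample-size section: "Therefore, in 18 months it will be 15%, which is the follow-up period forecasted in FRAILTOOLS project". All AUCs, sensitivities, specificities and completion rates below are assumptions. The sample size has no bearing on this point.

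**1. Value of each listed measure for a scale with no information.**
- AUC: 0.5.
- Likelihood ratio: 1.
- Positive and negative predictive value at 15% mortality: 0.15 and 0.85.
- Sensitivity or specificity: anything from 0 to 1, depending on how many people the rule calls positive.

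None is fixed at zero.

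**2. Break-even.** A scale with performance A and completion p loses to a rival with performance u and completion q when A × p < u × q, that is, when p/q < u/A.

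**3. AUC as the measure.**
- Useless scale, all evaluated: 0.50 × 1.00 = 0.500. Better scale: 0.70 × 0.70 = 0.490. The useless scale wins whenever the better one is completed by fewer than 0.50/0.70 = 71.4%.
- Weaker scale: 0.64 × 1.00 = 0.640. Better scale: 0.72 × 0.88 = 0.634. The weaker scale wins below 0.64/0.72 = 88.9% completion.

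**4. Which scale of the second pair is better over all patients?** Give each unevaluated patient a rank drawn at random from the evaluated patients' scores, with the same completion p in cases and non-cases.
- Pairs with both evaluated (share p²) are ordered correctly with probability AUC.
- The two kinds of mixed pair (share p(1 − p) each) have correct-order probabilities that sum to AUC + 0.5, whatever the prevalence.
- Pairs with neither evaluated (share (1 − p)²) score 0.5.

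Total: p² × AUC + p(1 − p)(AUC + 0.5) + 0.5(1 − p)² = 0.5 + (AUC − 0.5) × p.

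For 0.72 at 88%: 0.5 + 0.22 × 0.88 = 0.694, against 0.640 for the weaker scale. The two are equal at p = 0.14/0.22 = 63.6%. The index therefore picks the worse scale when completion of the better one lies between about 64% and 89%.

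**5. Sensitivity or specificity alone.**
- A scale calling everyone frail: sensitivity 1.00 × 1.00 = 1.00, against 0.85 × 0.95 = 0.81 for a real tool.
- A scale calling no one frail: specificity 1.00 × 1.00 = 1.00, against 0.90 × 0.95 = 0.855.

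**6. Other measures and models.**
- Negative predictive value: with sensitivity and specificity of 0.75 it is 0.6375/(0.6375 + 0.0375) = 0.944. This loses to the useless 0.85 below 0.85/0.944 = 90% completion.
- Positive likelihood ratio: 0.75/0.25 = 3.0 loses to 1.0 only below 33% completion.
- Adjusted models: a useless scale inherits the covariates' AUC. If that is 0.70, it beats a model with AUC 0.75 below 0.70/0.75 = 93.3% completion. If it is 0.65, it does so below 86.7%.

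**7. After re-zeroing.** (2 × AUC − 1) × p gives 0 for the useless scale, 0.28 × 1.00 = 0.280 for the weaker one and 0.44 × 0.88 = 0.387 for the better one. Because 0.5 + (AUC − 0.5) × p equals 0.5 plus half this index, it orders scales exactly as the all-patient AUC in step 4 does.

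**The case against.** The article never says that AUC enters the index. Since it ties screening to sensitivity and diagnosis to specificity, the nearer reading is sensitivity × proportion for one and specificity × proportion for the other. For screening that product has a sound meaning: the share of all cases detected, with unassessed patients counted as missed, if cases are assessed as often as non-cases. This stands, and weighting by feasibility is legitimate in itself. It does not rescue AUC or specificity, and it does not stop a rule that calls everyone positive from scoring 1.00.

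A different yardstick can also be proposed: settle every pair that includes an unevaluated patient by coin toss, giving p² × AUC + (1 − p²)/2. For the second pair that gives 0.670 and a misranking band of 80% to 89%, and (2 × AUC − 1) × p would then misrank from 64% to 80%. But this convention discards the evaluated patient's score in every mixed pair. A random rank from the observed scores keeps it and gives the linear result in step 4.

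A reader might infer that the plan will crown a useless tool, or that its main result is unsound. The documents do not support that. On unadjusted AUC a wholly useless scale wins only against a rival with low completion (under 71.4% for AUC 0.70), and no completion rates are given. Accuracy is also ranked on its own before the index is formed, and the secondary outcomes qualify each tool by several criteria. The primary outcome, the predictive value of each scale, does not use the index.

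**Conclusion.** The point holds as a defect in a stated decision rule. Followed as written, the index can place an uninformative or weaker scale above a better one, because the measure is unnamed and none of the candidates is fixed at zero for no information. The likelier harm is the misranking of a merely weaker scale: in the 0.64 against 0.72 example, an 11-point gap in completion is enough, and the error persists down to about 64%. The sizes rest on assumed AUCs and completion rates, on completion being equal in cases and non-cases, and on a random rank for unevaluated patients. It should be fixed. It is not critical, since accuracy and feasibility are also assessed separately and the index is not the primary outcome.

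**What to change.** In the Statistical analysis section, state which measure and which model enter the index, and put the measure on a scale where no information scores zero:
- Unadjusted model: (2 × AUC − 1) × proportion evaluated.
- Adjusted models: the gain in AUC over the covariate-only model in the same patients, × proportion evaluated.
- If separate screening and diagnosis rankings by sensitivity and specificity are kept, rank only scales whose chance-corrected performance is above zero. Use 2 × AUC − 1, or Youden's J where a cut-off exists; the article says the Gérontopôle tool has no clear one. State whether the estimate or its lower confidence limit must exceed zero, since an estimate will rarely be exactly zero.

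The cost is a few lines of wording and no new data. Index values will look smaller than the raw product. The entry condition removes rules that call everyone or no one frail, but a weak scale with a lenient cut-off can still lead on sensitivity alone, so sensitivity and specificity should be read together.

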Multiple studies have been undertaken worldwide to establish the prevalence of frailty [3, 7–9]. The data vary according to countries reaching a percentage of up to 27.3%. A survey of 7510 community-dwelling older adults in 10 European countries found that the prevalence of frailty was higher in southern than in northern Europe [7, 10]. For instance, in Spain the prevalence of frailty was 8.4% among institutionalized and community dwelling persons from rural and urban settings [8]. In Italy, in community-dwelling older adults the frailty prevalence was 13.9% [11]. In the French population older than 55 years-old and free of disability, around 25% are either frail or multimorbid [12]. In the nursing home setting this prevalence doubles in comparison with community dwelling people, reaching 68.8% according to a number of American studies [9, 13]. As frailty is highly associated with age, we should expect an increase in the number of new cases (incidence) of frailty as the European population gets older. Published data ranges from 4% new cases in adults aged over 65 years in Germany to 8% in adults aged over 60 years in Spain after three years of follow-up [14].

Dozens of scales and questionnaires have been used in the detection of frailty [15].; however a universal operational definition of frailty or a generalized method for its screening and diagnosis is still lacking [16]. In different clinical scenarios where the care of the elderly is a priority, such as primary health care or nursing homes, it is imperative to have specific instruments in the detection of frailty according to the characteristics of each level of care.

The FRAILTOOLS Project addresses the needs to validate scales for its application in different clinical and social settings, and its integration in management algorithms for the frail older patient.

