### Exclusion criteria

General exclusion criteria are:○ MMSE score ≤ 20 points.○ Terminal illness (life expectancy ≤6 months).A Barthel Index < 90 in patients from the Acute Geriatric Unit, Outpatient Geriatric Consultation and primary care centers.A Barthel Index < 40 in residents from nursing homes.

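### The best scale per setting is the largest of seven in-sample index values, with no allowance for selection or uncertainty, and the one validation step named does not test that choice.

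*Protocol article*

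**What the plan says.** All references are to the protocol article.

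- **Selection rule (Statistical analysis, first objective).** Each of seven scales enters logistic models per setting and per outcome: unadjusted, then with age and gender, then also with the Charlson index. Classification performance is computed for each model. The most sensitive tool is sought for screening and the most specific for diagnosis. Performance is then multiplied by the proportion of patients evaluated, and the scale with the largest product is declared best in that setting.
- **Validation (Statistical analysis, second objective).** To study assessment as patients move between settings, "we will first analyze the external validity of each model by using the data of each setting in the other models".
- **Sample structure (Recruitment process and sample size).** Five partners, one per country, recruit in all four settings: "every partner will be responsible for the enrolment, assessment and follow-up of 388 older adults (97 per setting"). Country appears in none of the three listed models and in no validation step.
- **Eligibility (Exclusion criteria).** Acute wards, outpatient clinics and primary care share one Barthel limit (below 90 excluded). Nursing homes have another: "A Barthel Index < 40 in residents from nursing homes".

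**The concern.** The first objective is to recommend a scale for each setting. Taking the largest of seven noisy values has two known effects: the winner's figure is too high on average, and the winner may not be the best scale. The remedy is to assess the selection step itself, by resampling or in other patients from the same setting. The one validation step the article names moves models to a different setting, so it cannot do this. The design nevertheless supplies five groups per setting, one per country, that could serve.

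At stake are the setting-specific detection algorithms listed among the secondary objectives. They would rest on one named scale with an overstated performance figure and no indication of how many other scales did about as well.

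**Working it through.** **1. The plan's own sample size, to fix the information per setting.** Inputs: a model of four variables, death at 15% over 18 months ("Therefore, in 18 months it will be 15%, which is the follow-up period forecasted in FRAILTOOLS project"), and 20% loss. Ten events per variable is an assumption, because the article names only the method; it gives 4 × 10 = 40 events. The rule is the smallest n for which the lower normal-approximation limit of the event count is at least 40:

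n × 0.15 − z × √(n × 0.15 × 0.85) ≥ 40

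- 95% (z = 1.960), n = 355: 53.25 − 1.960 × 6.73 = 40.1.
- 99% (z = 2.576), n = 388: 58.2 − 2.576 × 7.03 = 40.1.
- Loss: 388 / 0.8 = 485. Then 485 × 4 = 1940 and 485 / 5 = 97.

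This reproduces the stated result ("is 355 and 388 participants in each setting of care for 95 and 99% CI, respectively") exactly. The sample size is not in question. It was set for stable estimation of a four-variable model, not for ranking seven scales.

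**2. Information available for the ranking.**

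- Evaluable per setting: 485 × 0.8 = 388, with 388 × 0.15 = 58.2 expected deaths.
- Per country within a setting: 97 × 0.8 × 0.15 = 11.6 deaths.
- In four countries together: 4 × 11.64 = 46.6 deaths.

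**3. Behaviour of the maximum rule for death.** Assumptions: 388 people, 58 events, seven normally distributed scores with pairwise correlation 0.5 or 0.7, scale chosen by highest AUC. None of the correlations or AUCs is in the article.

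- Standard error of a single AUC: about 0.036.
- Standard error of a paired difference between two scales: about 0.03-0.04.
- All seven scales with true AUC 0.70: the winner's apparent AUC averages about 0.73-0.74, so 0.03-0.04 too high.
- Sensitivity at a common fixed cut-off, same set-up: about 0.65 for a single scale, and about 0.70-0.72 for the highest of the seven.
- One scale truly 0.03 better than the other six: chosen about 44-59% of the time.

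**4. Commoner outcomes.** The article says death is the least frequent of the four outcomes. At an assumed 40% event rate, the winner's optimism falls to about 0.02-0.03 and the truly better scale is chosen about 60-73% of the time.

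**5. What the cross-setting step can show.** Four settings form six pairs. The three pairs among acute wards, outpatient clinics and primary care share one Barthel limit. Only the three pairs with nursing homes differ, and nursing homes may also enrol residents with Barthel 90 or above, so the ranges overlap. None of the six pairs tests a setting's winner on new patients from that same setting.

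**The case against.** **The cross-setting step belongs to another objective.** This is correct. A reader might infer that the plan offers it as the check on the winning scale. It does not: the sentence opens the second objective, for which the step is suitable. What remains is that no other validation is named.

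**An unseen analysis plan may add resampling and intervals.** It may, and the silence of a condensed article is not itself the fault. But the article states a complete decision rule, an enumerated list of models and a named validation design. The point is about that rule as written.

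**The scales already exist, so there is little to overfit.** This largely stands. Fitting a positive slope to one score leaves its AUC unchanged, and the fullest models have about 58.2 / 4 = 14.6 deaths per parameter. The optimism is mainly from selection, which is what step 3 measures.

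**AUC is not the plan's index.** This is fair. The plan uses sensitivity or specificity and multiplies by the proportion evaluated, which may separate scales of similar accuracy. The performance factor is still in-sample, and the sensitivity figures in step 3 show the same upward shift.

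**Stronger readings that the documents do not support.**

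- *Cross-setting comparisons are confounded by eligibility.* The Barthel limit differs in only three of six pairs, and the ranges overlap.
- *Pooling countries materially distorts the AUCs.* The Background reports that "the prevalence of frailty was higher in southern than in northern Europe", but that comes from a ten-country community survey, not from these settings. The sample-size section calls the mortality differences among the five countries small. Any large distortion depends on country spreads that the article does not give.
- *Every model must contain a country term.* Four indicators would leave 58.2 / 8 = 7.3 deaths per parameter, and part of the model's AUC would then come from country instead of the scale. That trade-off is debatable and the omission is not an error.

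**Conclusion.** The concern holds for the selection rule. As written, the best scale per setting is an uncorrected in-sample maximum over seven candidates. The only validation named addresses a different question, and recruiting country is not used to test the within-setting choice.

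For death, the winner's AUC would be overstated by about 0.03-0.04, and a scale truly 0.03 better would be missed roughly half the time. For an outcome at 40%, the figures are about 0.02-0.03 and a miss in about 27-40% of cases (100 minus 60-73). These sizes rest on the assumed true AUC of 0.70, correlations of 0.5-0.7, and ranking by AUC. Clearer differences between scales, or in the proportion evaluated, would reduce the risk of a wrong choice.

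The sample size and the data collection are not affected. This is a should-fix point on how the winner is chosen and reported.

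**What to change.** **Main change, within each setting.**

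- Bootstrap the entire selection on the plan's own index, resampling within recruiting country.
- Report optimism-corrected performance for every scale and paired confidence intervals between scales.
- Name a single best scale only if its interval against the runner-up excludes zero. Otherwise report the tied set.

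**Supporting analyses.** Report country-stratified AUCs, and leave-one-country-out results pooled over the five rotations. Pooling is needed because a held-out country has only about 12 deaths in a setting. Define country by recruiting partner; the country of origin recorded on the case report form need not be the same.

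**Cross-setting step.** Keep it, labelled as transportability for the second objective, and note that only pairings with nursing homes differ in Barthel eligibility.

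**Cost.** Modest extra analysis and no new data. The real price is that some settings may end with no single winner.
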